#### Kinematic analysis

The variability of angular kinematics of the trunk and lumbar spine relative to the pelvic segment is primary interest of this study. A 3D kinematic measurement will be employed to verify the variability of trunk segment in 3 planes of movement relative to the pelvic segment. Previous studies have utilized the Winter’s coefficient of variation (CV) [58] to examine the consistency of movement patterns using the ensemble average of the raw waveforms of repeated trials [6, 15]. A new method of differentiating between the pattern and offset variability has been recently suggested. A large mean offset value effectively deflates the value calculated for variability using the CV [13]. Because of this, O’Dwyer et al. (2009) have suggested the use of methods to differentiate the offset from calculation of the variability in the waveform pattern, the latter being better representative of motor performance repeatability whereas the offset incorporates a greater degree of other variance sources (i.e. marker error). The offset values may also be affected by the reference posture that subjects adopt in each measurement session. Measurement of the reference position may be influenced by the identification of anatomical landmarks and joint centers of rotation, by the markers used, their configuration and their placement on anatomical landmarks. In contrast to offset variability (CVo), waveform pattern variability (CVp) is more manifestly distinguished by the repeatability of the motor performance and is less subject to factors related to reference position [3, 13, 45]. Furthermore, the between trial variability using CVp and CVo will be calculated for the trunk and the lumbar spine kinematics relative to the pelvis across planes of movement. CVp and CVo will be calculated using equations from O’Dwyer et al. [11]. In addition, peak displacement of the trunk movement in three planes will be calculated as the relative angles between the trunk and pelvic segments in three planes (i.e. frontal, sagittal and, transverse). Peak displacement of the lumbar segment will be calculated as the relative angles between the lumbar and pelvic segments in three planes (i.e. frontal, sagittal and, transverse) as described by Crosbie et al. [49].

Data will be normalized to 100% gait cycle and peak values for trunk and lumbar joints angle displacement and will be computed for each cycles and averaged for each subjects. Gait cycle will be considered to initial right heel contact (0%) and subsequent right heel contact (100%) and Heel contacts will be identified as the lowest vertical displacement of a right heel marker [3, 7].

#### Statistical analysis

Data will be analyzed using SPSS version 21 (SPSS Inc., Chicago, IL) software. The normal distribution of data will be analyzed by a Kolmogorov-Smirnov Z test. If the distribution is normal, the outcomes of the studied measurements will be evaluated the absolute change from pre- to post- for VAS, ODI and the kinematic variables using a paired T-test in CLBP group. To determine homogeneity of variances (i.e., variances approximately equal across groups), Levene’s test will be employed. In addition, to evaluate the kinematics variables between CLBP and healthy group, an independent samples T-test will be used to reveal any difference between two groups. A non-parametric test will be used if the data are not normally distributed to compare across two groups (healthy and CLBP) using a Mann Whitney U exact test and, a Wilcoxon signed rank exact test will be used to compare of the variables in pre and post intervention in CLBP. A *p*-value of less than 0.05 will be considered statistically significant. According to the Raymond et al. study [59] minimal change that can be considered with perceived pain questionnaire and ODI in low back pain are clinically useful for interpretation of results. Results of VAS and ODI will be compared with range of minimal important change (MIC) value for pain (15.0–20.0 points) and ODI (10.0–12.0 points) [59].

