### Participants

As there is no previous work to estimate the effect size for the kinematic variables considered here, we will conduct a pilot study to compute and estimate the effect size. Then, using power analysis, the required sample size with a power of 0.8 and an α of 0.05 will be determined. Assuming a large effect size, we anticipate recruiting 30 participants (15 in each group) for the study. Both males and females will be recruited in the study. The enrolment will be continued to reach the required sample size. Table 1 summarizes the inclusion and exclusion criteria for the CLBP group. Since the lumbar and trunk kinematics were not different during gait in the movement-based subgroups of NCLBP in a recent study [8], therefore in this study we will examined the NCLBP group regardless of their movement-based classification. Fifteen Healthy non-athlete subjects with no previous history of LBP will be included. Each healthy subject will be matched to a subject with LBP based on the age, sex, height, weight and BMI. In this group, subjects with a history of fracture, trauma and, pain of any other joints in the past also will be excluded from the study. In both groups participants will be excluded from the study if they have BMI higher than 30. Harsted et al. reported that CLBP with a BMI higher than 30 exhibited less variable and lower mean frontal plane range of motion compared to participants with a BMI below 30 [46]. However, less variability of movement of the trunk in this group is generally dependent to larger body mass instead of spine function [46].

**Table 1 Tab1:** Inclusion and exclusion criteria for the CLBP

Inclusion criteria	Exclusion criteria

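### If run uncorrected on 15 values, the Kolmogorov-Smirnov Z test that chooses between t-tests and rank tests has almost no power to detect skew; fix the test in advance or use a working check

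*Protocol article*

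**What the plan says.** The Statistical analysis section sets a two-step rule for all outcomes. First, "The normal distribution of data will be analyzed by a Kolmogorov-Smirnov Z test". If normality is accepted, pre-post change in the patient group is tested on the absolute scale with a paired t-test, and patients are compared with healthy subjects by an independent-samples t-test. Otherwise, "A non-parametric test will be used if the data are not normally distributed": an exact Mann-Whitney test between groups and an exact Wilcoxon signed-rank test within patients.

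The software is SPSS version 21. The section names neither a Lilliefors correction nor a transformation. It does not say whether the check is run in each group, on both groups pooled, or on the pre-post differences.

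Under Participants, "Assuming a large effect size, we anticipate recruiting 30 participants (15 in each group) for the study". This number is provisional, because a pilot is to set the final size. Under Kinematic analysis, movement variability, measured by CVp and CVo, is the primary interest. The article says nothing about how these measures are distributed.

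**The concern.** The rank tests are there to protect against non-normal data, and they are used only if the first test rejects. The ordinary Kolmogorov-Smirnov reference distribution assumes that the mean and SD are known beforehand. When both are estimated from the same 15 values, the fitted curve follows the sample and the test statistic is systematically too small for that reference. The test then almost never rejects, and the rule in effect always chooses the t-test.

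CVp and CVo cannot be negative, so right skew is plausible. If it is present, a raw-scale t-test on 15 per group can have less power than the rank test that the plan itself names. The rule also leaves open what is tested, and the answer changes how often the rank tests are used.

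**Working it through.** **Inputs.** From the article: 15 per group, power 0.80, alpha 0.05, and the tests named above. Assumed: two-sided tests; an uncorrected gate at the 5% level; lognormal CVp and CVo with log-SD 0.3 to 1.0. These log-SDs correspond to between-subject coefficients of variation, √(exp(s²) − 1), of 31%, 53%, 87% and 131% at 0.3, 0.5, 0.75 and 1.0.

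**1. The plan's own figure.** The article gives no number for a large effect, so 0.8 is assumed.
- Paired t-test, dz = 0.8: n = 14.3, rounded up to 15, with power 0.82. The figure of 15 reproduces.
- Two-group t-test, d = 0.8: 26 per group are needed, and 15 per group give 56% power. The figure of 15 does not reproduce. That is a separate matter. At 15 per group, 80% power needs d = 1.06, which is used below.

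**2. Critical values at n = 15.** The uncorrected 5% point of Z = √n × D is about √(−ln(0.025)/2) = 1.358. The test therefore rejects only if D > 1.358/√15 = 0.351. With mean and SD estimated, the correct (Lilliefors) 5% point, found by simulation, is 0.219. The uncorrected threshold is 0.351/0.219 = 1.6 times too high.

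**3. How often normality is rejected** (simulated)

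| Distribution | Uncorrected, n = 15 | Lilliefors, n = 15 | Shapiro-Wilk, n = 15 | Uncorrected, 30 pooled (no group difference) |
|---|---|---|---|---|
| Normal | 0.0% | 5% | 5% | 0.0% |
| Lognormal, log-SD 0.3 | 0.05% | 13% | 18% | 0.3% |
| 0.5 | 0.4% | 26% | 37% | 3% |
| 0.75 | 2.3% | 47% | 66% | 15% |
| 1.0 | 7.4% | 66% | 83% | 39% |

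If rejection in either group triggers the switch, the rate is 1 − (1 − p)². For log-SD 0.5, 0.75 and 1.0 this is 1 − 0.9964² = 0.7%, 1 − 0.9766² = 4.6% and 1 − 0.9265² = 14%. Direct simulation of the two-group comparison agrees (0.8%, 4.5%, 14%).

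**4. Power of the gated rule against the plan's own rank tests.** The two-group columns use a log-scale d of 1.06, with either group triggering the switch. The paired columns use a log-scale dz of 0.8, pre-post correlation 0.5, with the gate on differences.

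| Log-SD | Two-group: gated | Mann-Whitney | Loss | Paired: gated | Wilcoxon | Loss |
|---|---|---|---|---|---|---|
| 0.3 | 0.783 | 0.765 | none | 0.795 | 0.788 | none |
| 0.5 | 0.755 | 0.764 | 1 point | 0.750 | 0.767 | 2 points |
| 0.75 | 0.702 | 0.762 | 6 points | 0.678 | 0.748 | 7 points |
| 1.0 | 0.661 | 0.760 | 10 points | 0.600 | 0.731 | 13 points |

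Other settings shift these losses. With correlation 0.8 the paired losses at 0.5, 0.75 and 1.0 are 3, 9 and 15 points. With a two-group d of 0.8 they are 1, 5 and 8 points.

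**5. Type I error.** The gated rule stays between 0.034 and 0.051 in all null scenarios.

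**6. A Shapiro-Wilk gate instead**, on within-group values and on paired differences, at log-SD 0.3 / 0.5 / 0.75 / 1.0:
- Two-group power 0.80 / 0.79 / 0.77 / 0.76, against 0.79 / 0.76 / 0.70 / 0.66 for the Kolmogorov-Smirnov gate in the same runs.
- Paired power 0.81 / 0.77 / 0.74 / 0.72, against 0.80 / 0.75 / 0.67 / 0.61.
- Type I error near 0.05.

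**The case against.** The strongest reply is that the harm rests on an assumption. The article does not say that CVp or CVo are skewed, or by how much, and at log-SD 0.3 the gated rule does slightly better than the rank tests. This stands: the loss is conditional and its range starts at zero.

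Second, the article does not state that the test is uncorrected or that it is run on 15 values at a time. With the Lilliefors correction the gate rejects 26% to 66% at log-SD 0.5 to 1.0, and with 30 values pooled it rejects 3% to 39%. This also stands, so a reader should not infer that the rank tests will go nearly unused whatever the analyst does. It also shows that the rule as written leads to quite different analyses.

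Third, 15 per group is provisional, and the word used for what is tested (data) does not exclude testing the differences, since the next sentence concerns absolute change. Both are fair. But testing the differences does not rescue the uncorrected gate: with correlation 0.5 it rejects in only 0.2%, 1.9% and 7.2% of paired samples at log-SD 0.5, 0.75 and 1.0.

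Finally, one might compare the rule with a log-scale t-test and find larger losses (4, 10 and 13 points in the two-group case). That comparison is tilted, because the log scale is optimal by construction for lognormal data. In a different model, an SD over three trials with little spread between persons, the raw t-test beat the log-scale test (0.81 against 0.74). The documents do not support requiring a log transform.

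**Conclusion.** The point holds in conditional form. If the Kolmogorov-Smirnov Z test is run without correction on about 15 values, its true size is near 0% and it cannot do the job the plan gives it. The consequence is a possible loss of power, not false positives. Under assumed lognormal outcomes, the loss against the plan's own rank tests in the main scenarios is none at log-SD 0.3, 1 to 2 points at 0.5, 6 to 7 at 0.75 and 10 to 13 at 1.0. It is somewhat smaller or larger with other effect sizes and correlations.

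A reader might infer that the main outcomes are skewed, that power will be lost, or that the results would be invalid. The documents support none of these: they give no distribution, and the t-tests keep their type I error in these simulations. Severity is minor and confidence moderate. The gate's weakness is firm, while the size of the harm depends on data not yet seen.

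**What to change.** Remove the Kolmogorov-Smirnov Z gate and choose one of two replacements:

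- **(a)** Name the exact Mann-Whitney and exact Wilcoxon tests, already in the plan, as the primary tests for CVp and CVo, with the t-tests as a fixed sensitivity analysis. The test then no longer depends on the data.
- **(b)** If a check is kept, use Shapiro-Wilk, and state that it is applied to the pre-post differences for the paired test and to the values within each group for the group comparison.

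A log scale is optional and should be fixed in advance only if the planned pilot data support it.

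The cost is about two sentences. Under (a), the rank tests give up about 1 to 2 points of power when skew is mild (0.783 against 0.765 two-group and 0.795 against 0.788 paired, at log-SD 0.3). Under (b), the choice of test still depends on the data, and mild skew is often missed (63% of samples at log-SD 0.5). A log scale would report ratios in place of the absolute change that the article now plans.

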It is possible that the trunk stiffness, and altered lumbar and trunk kinematics including higher movement variability and lower displacement are a manifestation of commonly associated core muscles dysfunction [9]. Core muscles dysfunction can contribute to the poor motor control during gait that may result in compensatory trunk stiffness [19]. To the best of authors’ knowledge, the effect of isolated core training program on the between-trial variability and displacement of the trunk has not been investigated yet. On the other hand, the effect of an anterior load carriage task that is disruptive for LPS to alter the trunk movement pattern has not evaluated in previous studies. Thereby, previous studies have failed to reveal the effect of specific core training program on the lumbar, and trunk kinematics including between-trial variability as well as peak displacement during gait including anterior load carriage.

The study hypotheses are as follows:NCLBP group shows a lower between-trial variability and peak displacement of the trunk movement relative to the pelvis in the sagittal, frontal and transverse planes during gait with and without load compared to healthy.NCLBP group shows a lower between-trial variability and peak displacement of the lumbar movement relative to the pelvis in the sagittal, frontal and transverse planes during gait with and without load compared to healthy.Core stabilization exercise therapy increases the between-trial variability and peak displacement of the trunk relative to the pelvis in the sagittal, frontal and transverse planes during gait with and without load in NCLBP.Core stabilization exercise therapy increases the between-trial variability and peak displacement of the lumbar relative to the pelvis in the sagittal, frontal and transverse planes during gait with and without load in NCLBP.

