## Methods

### Study aims

The primary aim of this study is to evaluate the effect of 16-sessions core stabilization program on pain, disability and the spine kinematics while subjects walking with self-selected speed in subjects with NCLBP and comparison with healthy subjects.

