## Results

Demographic characteristics of participants will be illustrated in the first table. Duration of LBP, VAS and ODI will be included in the Table 2 for the NCLBP group. Other results will be reported in separate tables.

**Table 2 Tab2:** Demographic and clinical characteristics of study participants

	group		mean ± SD	*P* value
Gender	CLBP	Male		
		Female		
	Healthy	Male		
		Female		
Age (years)	CLBP			
	Healthy			
Weight (kg)	CLBP			
	Healthy			
Height (cm)	CLBP			
	Healthy			
BMI (kg/m2	CLBP			
	Healthy			
	mean ± SD			
Duration of LBP (month) VAS ODI	CLBP			

Values are mean ± standard deviation

Significant set at *P* ≤ 0.05

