## Discussion

The present study will investigate the effect of core stabilization exercise on the trunk, lumbar and pelvis kinematic in NCLBP during gait while carrying a load by hands. Based on the previous studies, gait deficiencies can be a symptom following CLBP [3, 8, 45]. Some researchers reported that people with CLBP exhibit less sagittal and transverse plane coordination variability of trunk-pelvis compared to healthy [10, 16–18, 20, 60], other finding revealed that the variability of lumbar kinematic during treadmill walking increases in CLBP [6, 15]. A potential link exists between changes in the trunk and lumbar spine movement variability during gait and core muscles dysfunction [9, 19, 30]. Although, the kinematic changes following LBP have been investigated in several studies [6, 9, 15–18, 20], however there is a lack of study that evaluated the effect of core stability exercise on the trunk, lumbar and pelvis kinematic during gait. To the best of our knowledge, only one pilot study has evaluated the effects of trunk strength and stability training program on spine kinematic [43]. However, they did not determine the movement variability. Core stabilization exercise is the most frequent therapeutic regimen for physical therapy in patients suffering from NCLBP [35, 39, 61, 62]. In addition, no studies have evaluated the effects of core training on gait kinematic during an anterior load carriage task that can challenged the trunk kinematic.

The main result of this study will explore and discuss about the question of what is the effect of core training program on the movement variability and displacement in trunk and lumbar spine relative to the pelvis in NCLBP, specially the transverse plane movement variability of the trunk relative to the pelvis can be altered or no?

The authors also will discuss about the effect of hand-held load on the trunk, lumbar spine and pelvis kinematic during gait before and after the core stabilization training program.

The strength of our study is the measurement of between-trial variability of the trunk and lumbar kinematic (CV_o_ and CV_p_) that is better representation of repeatability of motor performance [3].

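### At least 74 tests share a flat 0.05 threshold and no single outcome or contrast is primary, so no one result carries the 5% error rate

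*Protocol article*

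**What the plan says.** The Statistical analysis section plans a paired test (or Wilcoxon) of pre-post change in patients for VAS, ODI and the kinematic variables, and an independent-samples test (or Mann-Whitney) of the kinematic variables between patients and healthy subjects. All are read against one threshold: a p-value "of less than 0.05 will be considered statistically significant".

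Three sections say what matters most:

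- Study aims: "The primary aim of this study is to evaluate the effect of 16-sessions core stabilization program on pain, disability and the spine kinematics", together with the comparison with healthy subjects.
- Kinematic analysis: "The variability of angular kinematics of the trunk and lumbar spine relative to the pelvic segment is primary interest of this study".
- Discussion: the main result concerns variability and displacement of trunk and lumbar spine, "specially the transverse plane movement variability of the trunk relative to the pelvis can be altered or no".

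On the two variability measures, Kinematic analysis says that pattern variability (CVp) is the better guide to how repeatable motor performance is, while the offset carries more variance from other sources such as marker error. The Discussion credits CVo and CVp together as a measurement "that is better representation of repeatability of motor performance".

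**The concern.** A 5% error rate belongs to one test named in advance. Here dozens of tests each receive 5%, and the sections disagree on whether pain, disability and displacement belong to the primary question at all. A later analysis plan could not honour all three descriptions.

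The four hypotheses in the Background do not settle it. Each covers variability and displacement, in three planes, with and without load. The one on training and the trunk begins "Core stabilization exercise therapy increases the between-trial variability and peak displacement of the trunk relative to the pelvis". None says how many of its components must succeed for the hypothesis to count as supported.

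At stake is how a reader can interpret a significant result. Without a named primary test, an isolated kinematic p-value below 0.05 could be put forward as the finding, and nobody could say what error rate stands behind it.

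**Working it through.** **Plan's own figure.** The only sizing statement is in Participants: "the required sample size with a power of 0.8 and an α of 0.05 will be determined", with 15 per group anticipated for an effect described only as large. No number of tests and no overall error rate is given. If large means a standardised effect of 0.8 (an assumption), one two-sided paired t-test at 0.05 and 80% power needs 14.3, so 15 patients, with power 0.82. The anticipated 15 therefore fits one paired test at 0.05.

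**Count of tests.**

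- Segments: trunk and lumbar, each relative to the pelvis = 2.
- Planes = 3.
- Measures: CVp, CVo, peak displacement = 3 (Kinematic analysis).
- Load conditions: with and without = 2 (Equipment).
- Kinematic variables: 2 × 3 × 3 × 2 = 36.
- Pre-post tests: 36 + VAS + ODI = 38.
- Patient-healthy tests: 36, counted once because no time point is given.
- Total: 38 + 36 = 74.

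Cross-check from the hypotheses: each covers 3 planes × 2 loads × 3 measures = 18 tests; 4 × 18 = 72, and adding VAS and ODI gives 74. This is a minimum. A second patient-healthy comparison after training makes 74 + 36 = 110. The baseline p-values in Table 2 and any direct test of load are not counted.

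**Expected false positives if no true difference exists anywhere.** 74 × 0.05 = 3.7, whatever the correlation between tests (110 × 0.05 = 5.5).

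**Chance of at least one.** If independent, 1 − 0.95^74 = 0.978. Correlation lowers this. A simulation of the same null used 15 per group, normal data, equal correlation between all outcomes, an assumed pre-post correlation of 0.6, and 10,000 runs:

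| Correlation between outcomes | All 74 tests | 36 pre-post kinematic tests only |
|---|---|---|
| 0 | 98% | 85% |
| 0.3 | 92% | 72% |
| 0.5 | 81% | 57% |
| 0.7 | 61% | 39% |
| 0.8 | 48% | 29% |
| 0.9 | 33% | 19% |

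**What correction would cost in power** (illustration only; effect 0.8 assumed, n = 15 per group):

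- One primary paired test at 0.05: 0.82.
- Bonferroni over all 74, 0.05/74 = 0.00068: paired 0.18, two-sample 0.08.
- Strictest Holm step within the 38 pre-post tests, 0.05/38 = 0.0013: paired 0.25.
- Strictest Holm step within the 36 patient-healthy tests, 0.05/36 = 0.0014: two-sample 0.12, against 0.56 for one unadjusted test.

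**The case against.** Several objections have force.

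- **Scope.** A multiplicity procedure is commonly left to an analysis plan, and a journal article condenses. That stands: silence on adjustment alone would be no finding. But the article is not silent. It fixes one threshold for all tests and describes the primary question in ways that differ.
- **Independence.** A reader might infer from the 98% that a chance finding is close to certain. The documents do not support that. The outcomes come from the same walks, segments and participants, so independence is the least plausible case, and no correlations are given. The figures also assume no true difference anywhere, while the Background cites earlier patient-healthy differences.
- **A third primary.** A reader might infer that the Discussion names transverse-plane trunk variability as a rival primary outcome. It does not; it stresses that plane within a wider set. The Kinematic analysis sentence can also be read as primary among kinematic measures. The firm mismatch is the status of pain, disability and displacement.
- **Conjunctive hypotheses.** Read literally, each hypothesis needs all its components, and demanding all of them does not inflate the error rate. So it goes too far to say that the trial cannot confirm or refute anything. The reading is possible, but the article does not state it.
- **VAS and ODI.** These are also set against minimal important change ranges, so 0.05 is not their only yardstick. That stands for two of the 74 tests.
- **CVo.** The contrast drawn in Kinematic analysis is one of degree, so this is a matter of consistent wording rather than an error rate.

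**Conclusion.** The point holds in this form: at least 74 tests at a flat 0.05, no single primary outcome or contrast, and sections that disagree on what is primary. Under a global null, 3.7 false positives are expected. The chance of at least one runs from 98% under independence to about 33% at a correlation of 0.9, and even the low end is more than six times 5%. The range rests on the simulation assumptions above; the count of 74 and the 3.7 do not depend on the correlation. The power figures rest on an assumed effect of 0.8, and the final sample size awaits the planned pilot.

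A reader might also infer that the plan favours unloaded walking as its main condition. It does not: every hypothesis covers both conditions, and the Discussion opens with gait under load.

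**What to change.** Before data collection:

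1. Reconcile Study aims, Kinematic analysis and Discussion, and name one primary outcome and one contrast, tested at 0.05. The candidate best supported by the text is pre-post change in CVp of the trunk relative to the pelvis in the transverse plane: Kinematic analysis prefers CVp, and the Discussion stresses that plane and segment. The load condition is for the sponsor to choose, and must be fixed in advance.
2. Treat VAS, ODI and the remaining kinematic variables as secondary, with Holm or false-discovery-rate control separately within the pre-post and patient-healthy families. Alternatively, treat them as exploratory, with confidence intervals and no significance claims.
3. State at which visit patients are compared with healthy subjects, since this decides whether that family has 36 or 72 tests, and state what counts as support for each four-part hypothesis set out in the Background.
4. Align the Discussion with Kinematic analysis, so that CVo is not presented as representing motor-performance repeatability as well as CVp does.

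The cost is protocol and registry wording and a few lines of analysis. Fewer results can be called significant, and power for any one secondary kinematic test falls. The single primary test keeps the full 5% level and, under the assumed effect, its 0.82 power.
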